#### Primary analysis

We will use a generalized linear mixed model (GLMM) using the time points immediately, 3 months, and 6 months after the treatment. The model will account for dependence of responses within individuals attributable to repeated measures. GLMMs will include random effects person ID and will be fitted using SAS PROC GLIMMIX with maximum likelihood estimation via adaptive quadrature with a minimum of 15 integration points. Nicotine vaping abstinence will be measured by 7-day point prevalence. Covariates will be sex as a biological variable and other variables that are found to be related to abstinence. If missing data is not negligible, we will use multiple imputation procedures to impute missing data. Data about biochemically verified abstinence will be analyzed using the same method as self-reported 7-day point prevalence of abstinence.

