### Sample size estimation

Power analyses were generated using the two-group repeated proportions module in NCSS PASS 14 [40] to compute minimum detectable effect sizes for the primary analysis. Assuming α = 0.05, power = 0.80, rho = 0.43 and a 7-day abstinence base rate of 3.2% and a quit rate of 8.3% in the treatment group from our preliminary data [31], group sample size of 234 (N_total_ = 468) is needed. Assuming a dropout rate of 7%, we need 500 participants.

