Participants who sign the consent form will be asked to create a login, and then redirected to the baseline assessment. This study will recruit 500 participants in total. Those completing the baseline assessment are randomized using a computer-generated random sequence which automatically assigns participants without revealing allocation to study investigators. Participants are assigned to either the Instagram intervention or the control condition, which is a referral to free support administered by the California quitline via the website kickitca.org. Approximately two weeks after the first participant is enrolled in an intervention group, the group will begin to receive the intervention program. Groups may start slightly sooner or later than 2 weeks based on the pace of recruitment, aiming for a group size between 5 – 15 participants. Depending on the pace of enrollment, multiple groups may run simultaneously.

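### Only the intervention arm is treated in interacting groups of 5–15, but the primary model and the sample size allow for dependence within a person only; any variation between groups makes the treatment standard error too small

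*Protocol article*

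**What the plan says.** All references are to the protocol article.

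- **Study procedure.** Participants are randomized individually. Intervention participants then enter groups that start about two weeks after the first member enrols, with timing "based on the pace of recruitment, aiming for a group size between" 5 and 15. Several groups may run at once.
- **Intervention group** and **Discussion.** A trained Guide facilitates and sends the daily posts, which are meant to draw responses. The Discussion expects daily interaction among members and describes this age range as more open to peer influence.
- **Control group.** Controls are pointed to a website. No groups are described.
- **Primary analysis.** "The model will account for dependence of responses within individuals attributable to repeated measures". The model specification is "GLMMs will include random effects person ID and will be fitted using SAS PROC GLIMMIX". No group effect or cluster-robust variance is mentioned.
- **Sample size estimation.** "Power analyses were generated using the two-group repeated proportions module in NCSS PASS 14", with the inputs "Assuming α = 0.05, power = 0.80, rho = 0.43", "a 7-day abstinence base rate of 3.2"% and 8.3% under treatment. The result is 234 per arm (468), raised to 500 for 7% dropout. No group size, ICC or design effect appears.

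**The concern.** This is a partially nested design: individuals are randomized, but one arm is treated in groups and the other is not. With about 250 people in the intervention arm and a mean group size of 10, there are about 25 groups (250 / 10).

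Members of a group can influence each other's quitting, and they share an enrolment period. If this makes abstinence differ between groups, members' outcomes are correlated. A random intercept for the person does not absorb this, because it still treats two members of the same group as independent. The variance of the intervention-arm estimate is then understated. The confidence interval is too narrow, the test rejects too often, and the stated power does not describe a valid analysis. A positive trial could be challenged on this point.

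**Working it through.** **Inputs from the article.** Rates 3.2% and 8.3%; α = 0.05 (taken as two-sided); power 0.80; rho = 0.43; 234 per arm; groups of 5 to 15, in the intervention arm only; three follow-ups.

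**Assumed.** ICC 0.01, 0.02 and 0.05 (the article gives none); mean group size k = 10, with 15 as the upper case.

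**Step 1: reproduce the stated size.** The two-proportion formula with pooled variance under the null gives 326 per arm at one time point. Averaging M equally correlated assessments multiplies this by f = (1 + (M − 1) × 0.43) / M.

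- M = 2: f = 0.715; 326 × 0.715 = 233.1, rounded up to **234**. This is an exact match, with power 0.802.
- M = 3: f = 0.62; 326 × 0.62 = 202.1, rounded up to 203. At 234 per arm, power is 0.854.

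The stated figure is therefore what independent participants and two assessments give. Three follow-ups are planned, so both bases are carried forward.

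**Step 2: add the groups.** Multiply the intervention-arm variance by a design effect DE and leave the control arm unchanged. Two versions bracket the answer:

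- simple: DE = 1 + (k − 1) × ICC
- group effect constant over assessments: DE = 1 + (k − 1) × ICC / f

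Under the null, with equal arms, true SE / model SE = √((1 + DE) / 2), and the true type I error is 2 × (1 − Φ(1.96 / √((1 + DE) / 2))).

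Example, k = 10, ICC 0.05, simple: DE = 1 + 9 × 0.05 = 1.45; SE ratio √1.225 = 1.107; 1.96 / 1.107 = 1.77; type I error 7.7%. With a constant group effect and M = 3: DE = 1 + 0.45 / 0.62 = 1.726; SE ratio 1.167; type I error 9.3%.

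**Step 3: results at k = 10 and 234 per arm.** Ranges run over the two versions of DE. Type I error also runs over M = 2 and M = 3.

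| ICC | Type I error of person-only model | Power of a valid test, M = 2 | Power of a valid test, M = 3 |
|---|---|---|---|
| 0 | 5.0% | 80% | 85% |
| 0.01 | 5.5–5.8% | 77–78% | 83–84% |
| 0.02 | 6.0–6.7% | 75–76% | 80–82% |
| 0.05 | 7.7–9.3% | 68–71% | 72–77% |

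At k = 15 and ICC 0.05, type I error is 9.2% to 11.7%.

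**Step 4: how large is an ICC of 0.05 here?** On the observed scale, between-group SD = √(ICC × p × (1 − p)). At p = 0.032:

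- ICC 0.05: √(0.05 × 0.032 × 0.968) = 3.9 percentage points, more than the mean rate itself.
- ICC 0.01 and 0.02: 1.8 and 2.5 points, or 55% and 78% of the mean.

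At p = 0.083, ICC 0.05 gives 6.2 points. So 0.05 is a high value at these event rates.

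**The case against.** **Power.** A reader might infer that the 80% power statement simply fails. The documents do not support that. If all three planned assessments contribute, power at 234 per arm starts at 85% and stays near or above 80% up to an ICC of about 0.02 at group size 10. The statement fails at these lower ICCs only on the two-assessment basis. That basis reproduces 234, but the article does not state it.

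**Mechanism.** A reader might also point to the shared Guide and posts as a source of clustering. As described, these are common to every group, so they belong to the average treatment effect and create no variance between groups. Only interaction within a group and differences between enrolment cohorts can do so. The content is built mainly on cognitive behavioural skills and quit planning, so how strong the peer effect will be is open.

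**Null hypothesis.** If the programme affects nobody, group interaction changes no outcome and inflates nothing. The inflation from interaction arises when group effects exist but average to zero. This narrows the type I error claim. It does not rescue the confidence interval when the programme works in some groups more than others.

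**Unseen documents.** The article condenses a fuller plan, and saying that a model will include a person effect does not strictly exclude others. This carries less weight, because the same section describes dependence within individuals only and the power inputs show no group term.

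**Feasibility.** At 8.3% and ten per group, a group yields about 0.8 abstainers per assessment. A group variance estimated from about 25 such groups will be imprecise and may come out as zero. This stands, and the remedy has to provide for it.

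**Conclusion.** The concern holds in conditional form. The stated primary model and sample size ignore group dependence in the one arm that has groups. For any positive ICC arising from peer interaction or enrolment cohort, the standard error is too small; at ICC 0 nothing is lost.

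The size rests on an assumed ICC. It is modest at 0.01 to 0.02 and material at 0.05, which is high for these rates. Whether power falls below 80% depends on that ICC, on group size and on how many assessments inform the estimate, so an unconditional claim that the trial is underpowered is not supported. Severity: should be fixed.

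**What to change.** Before outcome data are seen:

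1. Specify the primary GLMM as partially nested, with the person effect kept and a random effect for Instagram group acting in the intervention arm only.
2. State a fallback in case the group variance is estimated at zero or the model does not converge: standard errors clustered by Instagram group, controls as singletons, with a small-sample correction for the number of groups.
3. Apply the same rule to the secondary outcomes.
4. Restate power over a range of ICCs and the planned group sizes of 5 to 15, and say how many assessments the calculation uses. No extra enrolment is proposed.

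The cost is a change of wording and one model term. The study itself assigns the groups, so membership is known. The downsides are slightly wider intervals, a less favourable stated power and an imprecise estimate of the group variance.

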### Baseline measures

Baseline measures will consist of sociodemographic characteristics, nicotine vaping, quitting experience, motivations to quit (such as readiness to quit vaping, confidence in ability to quit, desire to quit, and commitment to abstinence), other tobacco use, marijuana/cannabis use, social media use integration, and symptoms of depression or anxiety.

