### Data analysis

Descriptive statistics will summarize sample characteristics and intervention delivery in each group. We will examine treatment condition and baseline descriptive characteristics as predictors of attrition at intervention end and will control for predictors of attrition as covariates in model testing. Missing data will be minimized through online assessment, and subjects will be re-contacted through social media or email to obtain missing information. Two sets of outcome analyses will be conducted: one self-reported by all participants who are maintained in the study, and another based on biochemically verified abstinence rates.

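### Beyond sex, the primary model's covariates are chosen from observed abstinence and attrition, so the primary analysis is not fixed before outcomes are seen

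*Protocol article*

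**What the plan says.** The Primary analysis section of the protocol article states the model: "We will use a generalized linear mixed model (GLMM) using the time points immediately, 3 months, and 6 months after the treatment". A person-level random effect handles the repeated measures. On covariates it says: "Covariates will be sex as a biological variable and other variables that are found to be related to abstinence".

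The Data analysis section adds a second route into the model. It first says "We will examine treatment condition and baseline descriptive characteristics as predictors of attrition at intervention end", and then that the analysis "will control for predictors of attrition as covariates in model testing".

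The Baseline measures section shows what is available at entry: "Baseline measures will consist of sociodemographic characteristics, nicotine vaping, quitting experience, motivations to quit", followed by other tobacco and cannabis use, social media use, and depression or anxiety symptoms. The 50% reduction outcome (Secondary outcomes) multiplies vaping days by puffs per day and compares with baseline, so a baseline vaping amount must exist. None of these is named as a covariate. Because the response uses only post-treatment assessments, baseline vaping does not enter as a response either.

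**The concern.** This is a stated rule, not a detail left out. It makes the content of the primary model depend on the primary outcome. Several things stay undecided until the data are in hand:

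- which variables are candidates, and which test and cut-off admit them;
- which form of abstinence is screened (self-reported or verified) and at which of three assessments, which already gives 2 × 3 = 6 possible screens;
- whether candidates are limited to baseline. Read literally, quit attempts or cessation strategies used after randomisation could qualify, and adjusting for them could remove part of the treatment effect;
- how the attrition predictors, screened at intervention end only, combine with the abstinence predictors.

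The odds ratio from a logistic model is conditional on the covariates in it, so the quantity reported is also unsettled. The person random effect already conditions on stable differences between people, so this shift may be smaller than in ordinary logistic regression. The documents do not allow it to be sized.

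At stake is the credibility of the primary result. If the adjusted and unadjusted analyses fall on different sides of 0.05, nothing in the article shows which was the planned one.

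**Working it through.** **1. The plan's own sample size.** Inputs from Sample size estimation: p1 = 0.032, p2 = 0.083, α = 0.05 (two-sided assumed, as sidedness is not stated), power 0.80, rho = 0.43. Mean rate p̄ = (0.032 + 0.083)/2 = 0.0575.

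For one assessment:

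n = [1.960·√(2·0.0575·0.9425) + 0.842·√(0.032·0.968 + 0.083·0.917)]² / 0.051² ≈ 326 per group.

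Multiply by the repeated-measures factor [1 + (M − 1)·rho]/M:

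- M = 2: 326 × 0.715 = 233.1, so 234, the stated figure.
- M = 3: 326 × 0.62 = 202.1, so 203. With a continuity correction, 365 × 0.62 = 226.3, so 227.

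Dropout: 468/0.93 = 503.2 and 468 × 1.07 = 500.8, both close to the stated 500. The calculation uses no covariates, so nothing below changes the sample size.

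**2. Events available to the model.** Expected abstinent participants per assessment:

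- 234 per group: 234 × (0.032 + 0.083) = 26.9
- 250 per group: 250 × 0.115 = 28.75

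Three assessments at rho = 0.43 carry about 3/(1 + 2 × 0.43) = 1.6 times the information of one, so these counts understate what the full model has.

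**3. Effect of the rule.** The documents give no association between any covariate and abstinence, so a range is assumed. Logistic regression at one assessment, 468 participants, ten independent candidate covariates, 3,000 simulated trials per setting. The first covariate stands for baseline vaping. Screening means p < 0.05 against the outcome, pooled over groups. The last column keeps the most favourable of the four preceding models.

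Type I error (5.75% abstinent in both groups):

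| Log-odds per SD: vaping; other nine | Unadjusted | Fixed vaping | Screened | All ten | Best of four |
|---|---|---|---|---|---|
| 0; 0 | 5.2% | 5.1% | 5.2% | 5.3% | 6.1% |
| 0.5; 0.1 | 4.4% | 4.4% | 4.1% | 4.6% | 5.7% |
| 1.0; 0.1 | 5.3% | 5.2% | 5.1% | 5.6% | 7.7% |

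Rejection rate at 3.2% vs 8.3%:

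| Log-odds per SD: vaping; other nine | Unadjusted | Fixed vaping | Screened | All ten | Best of four |
|---|---|---|---|---|---|
| 0; 0 | 64.5% | 64.5% | 64.4% | 64.2% | 67.1% |
| 0.5; 0.1 | 66.0% | 66.3% | 65.9% | 66.5% | 70.8% |
| 1.0; 0.1 | 65.7% | 68.3% | 68.1% | 68.8% | 73.4% |

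A separate simulation of the same design, with stronger assumed associations (0.8–1.2 per SD), gave type I error of 4.2–4.7% unadjusted, 4.2–4.5% screened, and 5.1–6.0% when the better of those two is kept. Power was 65.6–66.7% unadjusted and 67.1–71.6% with the prognostic covariate fixed.

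The Monte Carlo standard error near 5% is √(0.05 × 0.95/3000) = 0.4 points.

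**4. Reading the results.**

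- Mechanical screening: 4.1–5.2%, so no inflation.
- Free choice: about 5–6% with two models, 6–8% with four sets.
- Fixed versus screened power: +0.1, +0.4 and +0.2 points, which is negligible.
- Fixed versus no adjustment: 0, +0.3 and +2.6 points in the tables. In the stronger settings, matching low end with low end and high with high, 67.1 − 65.6 = 1.5 and 71.6 − 66.7 = 4.9. The range is about 0 to 5 points.

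**The case against.** The strongest reply is that the rule, applied as written, does no measurable harm. Screening held type I error near 5%, and a strong predictor would be found and included anyway, so almost no precision is lost. The inflated figures need an analyst who fits several models and keeps the best, which the article does not describe. All of that stands, and it limits the point to flexibility.

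Other stronger readings that a reader might infer also lack support:

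- *The covariate set is wholly open.* It is not; sex is fixed.
- *The model would be overloaded.* Events are few, but even all ten covariates gave type I error of 4.6–5.6%. Bias in the odds ratio was not examined.
- *An unblinded analyst picks the covariates.* The article does not say whether the analyst is blinded. Study procedure says only that assignment does not reveal allocation to investigators.
- *Adjusting for attrition predictors is an error.* Conditioning a likelihood-based mixed model on baseline predictors of missingness is a recognised way to make missing-at-random more plausible. The weakness is that these predictors reselect the primary model after data are seen.

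The simulations cover one assessment with assumed associations, not the three-assessment mixed model, and omit sex and the attrition screen.

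Finally, an analysis plan that is not shown may give the candidate list and threshold. That would close much of the gap. But a plan with a fixed set would have to depart from what the article says, so the two would still need to be aligned.

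**Conclusion.** The point holds as one about analytic flexibility. The article makes the covariates of its primary model, apart from sex, depend on observed abstinence and observed attrition, without a candidate list, threshold, time point or restriction to baseline. The primary analysis is therefore not fixed until outcomes are seen.

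The size is modest: no inflation if one screening rule is applied mechanically, about 5–6% if an analyst could keep the better of two models, and about 6–8% with four covariate sets. A reader might infer a real loss of power. The comparison that matters, fixed against screened, shows at most 0.4 points, and only the comparison with no adjustment reaches about 5. These figures rest on assumed log-odds of 0 to 1.2 per SD and on a single assessment. The finding that the rule is open does not depend on them. It should be corrected because doing so costs almost nothing before outcomes are analysed.

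**What to change.** Before any outcome data are examined, replace the covariate rule in Primary analysis, and in the analysis plan, with a short closed list of baseline variables already collected:

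- sex;
- baseline vaping amount (days × puffs per day);
- at most one motivation measure, named in advance.

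With treatment that is four terms before time effects, or 26.9/4 = 6.7 to 28.75/4 = 7.2 abstinent participants per term at each assessment. Five covariates plus treatment would leave 26.9/6 = 4.5 to 28.75/6 = 4.8, so the list should stay short.

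State that no post-randomisation variable is used as a covariate, and that the same set applies to self-reported and verified abstinence. Use baseline predictors of attrition in the multiple imputation model, which the article already foresees, or in a labelled sensitivity analysis, so that they do not reselect the primary model. Report the model without these covariates alongside.

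Cost: a few sentences, with no new data and no change to the sample size. A fixed covariate that turns out weakly prognostic costs a little with so few events. In the simulation with no association, one such covariate showed no loss (64.5% either way) and all ten lost 0.3 points (64.5% to 64.2%).

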#### Secondary analysis

We will estimate and test mixed effects logistic and multinomial regression models for longitudinal ordinal response data to model secondary outcomes for vaping over time: 1) vaping reduction by 50% or more; 2) vaping quit attempts; 3) readiness to quit vaping; 4) confidence in ability to quit; 5) desire to quit; 6) commitment to abstinence (i.e. endorsing the personal goal of wanting to quit nicotine completely); and 7) use of evidence-based cessation strategies.

### Ethics approval

The study protocol was submitted for ethics approval to WCG IRB, a trusted partner to more than 3,300 research institutions ranging from small community hospitals and research sites to large academic medical centers and universities in the United States. WCG IRB approved this study on August 27, 2021. The protocol is registered with ClinicalTrials.gov (protocol #NCT04707911).

### Research dissemination

Findings of this study will be disseminated to educators and researchers through publications in peer-reviewed journals, presentations at national or international conferences, and sharing in seminars. In addition, we will share results with community partners for this trial including but not limited to reports and meetings with the California Department of Education Tobacco-Use Prevention Education Program and associated programs, the Stanford Tobacco Prevention Toolkit, and partners at the San Francisco Department of Public Health Tobacco Free Project and the California Tobacco Control Program.

## Discussion

This is the first clinical trial of a social media-based vaping cessation intervention for adolescents and young adults. As vaping among young people has become an urgent problem in tobacco control, our study is well timed to provide a rigorously evaluated evidence-based social media intervention to address the epidemic of adolescent and young adult vaping. Using social media platforms to implement the vaping cessation intervention for adolescents and young adults is pioneering. Given the nature of social media, including high use rates among young people and lack of geographic restrictions, the intervention has high potential to reach a large number of young people who vape, provide accessible support, and achieve large scalability. However, though a systematic review of social media interventions for smoking cessation observed greater abstinence, reduction in relapse, and increase in quit attempts [29], social media interventions reported high dropout rates and low engagement over time, which significantly reduced the intervention efficacy [28, 29]. To address this problem, the intervention has been developed with experts in human centered design and co-created by adolescents to maximize acceptability and engagement. We will also utilize state of the art strategies from prior longitudinal studies of adolescents and young adults to track study participants [50, 51].

While social media may be an ideal platform for behavior change interventions targeting adolescents and young adults, the open nature of the social media may comprise a potential threat to individual privacy and unintended information sharing. To protect the participant privacy to the fullest extent possible, the Principal Investigator ([name]) has obtained a Federal Certificate of Confidentiality to protect the data from subpoena, will make sure that the identifying information (e.g., IP address, email address) will be separated from survey responses, and will give assurances that participants’ e-mail addresses will not be sold or disseminated to any company or individual (participants have been informed of this in the consent form). In addition, group sharing and membership can be limited through privacy settings and individual users can choose who has access to their information. However, the privacy settings and security of material posted on Instagram is under control of Instagram, and thus subject to change should Instagram decide to do so. Therefore, the study investigators cannot guarantee complete privacy of material posted on Instagram. Moreover, at some point during the intervention a participant may share personal information (e.g., vaping quit date, ask for support with reduction or cessation from friends) with their larger social networks. When participants enter the study, they will be informed that the intervention may ask that they share information on social media, but they can choose whether to do so and which people see this information. If participants choose not to share information publicly on social media, it will be made explicit that there will be no consequences whatsoever. In our prior work with Facebook smoking cessation groups, we have not had any privacy concerns among our participants. Any concerns about privacy will be immediately addressed with participants privately.

This intervention is designed for adolescents and young adults, populations in the midst of a stage in life in which they are more susceptible to peer influence [52–54]. Previous studies found that 25% of teenagers aged 16–17 years old posted references to alcohol on their social media profiles [55]; in addition, substance use, violence, sexual behavior, and even suicidality are also commonly displayed on social media platforms [55–58]. This calls for more serious monitoring of daily interaction among the participants in our Instagram groups. First, before starting the groups, we will remind the participants that the focus of the group is on vaping experience and quit vaping efforts, and that interactions should be respectful. Second, we have a trained Guide in the groups, who will monitor the everyday conversation of the participants. If problematic content is spotted, the guide will remind the involved participants privately and report serious cases to the Principal Investigator for resolution and further actions, including study disqualification. One of our inclusion criteria is using social media ≥ 4 days per week. Previous studies have found that depression may be common among adolescents who spend a significant amount of time on online social networks [59]. Another study found that more than half of secondary school students experienced a need for mental health support [60]. Our team is ready to deal with mental health issues and/or with serious withdrawal symptoms such as sleep problems, irritability, or in the unlikely event that they become emotionally distressed as a result of answering assessment questions. The Principal Investigator, a Sub-Investigator, and the Study Physician in this team are all practicing clinicians with experience working with vulnerable populations, young people, and substance use. They can counsel study participants privately over email, or on the phone if necessary and make appropriate referrals to medical providers or mental health resources should participants reveal a need for such support.

This study is the first to implement a vaping cessation intervention for adolescents and young adults entirely through a social media platform and rigorously evaluate it. It is based on a previously tested social media-based intervention for young adult smokers and was developed with thoughtful, iterative, and participant-engaged adaptation. If effective, this study will provide one of the very first evidence-based social media interventions to address the urgent issue of vaping among adolescents and young adults. The program has already been adopted by health departments and other youth serving partners in South Carolina, Minnesota, the San Diego school districts, and Oklahoma, demonstrating it is feasible to deliver this accessible evidence-based support to a large number of adolescents and young adults interested in quitting vaping.

